**Figure 1 F1:**
[figure not shown]
**Inclusion flowchart**.

### Intervention and care as usual

The intervention will be ACTE, an integrated multidisciplinary treatment model. It will have four main components: 1.) the caseload will be both small and shared (10 patients per case manager), 2.) services and assertive outreach will all be community based, 3.) all services (i.e. both medical and psychosocial) will be provided by the ACTE team, and 4.) and all services will be provided on an unlimited basis [25-27].

ACTE has been described in a manual that describes the target group, the team's working method, and tasks of the various disciplines involved. It also includes various programmes (modules) based on other evidence-based practices. Under ACTE, care is given with regard to various essential life domains, at whichever location the patient is [28]. Professional mental healthcare workers invest in a long time relationship with the patient, even if he or she initially continues to refuse care.

To address the most common problems of the target group, the ACTE team will represent several disciplines (table 1), and will have ten full-time equivalents working force. The low caseload will allow for intensive contact with patients. Team members will collaborate closely on each patient, using one treatment plan.

**Table 1 T1:** Differences between ACTE and CAU

Intervention Group (ACTE)	Control Group (CAU) Gerontology psychiatry teams	Control Group (CAU) Psycho geriatric team
A shared caseload (all care providers know all the patients and work together in the treatment).	Individual care providers responsible for patient assessment and for coordination and treatment.	Individual care providers responsible for patient assessment and for coordination and treatment.
A low caseload (a maximum of ten patients in the team per individual care provider).	A high caseload for the individual practitioner (> 20).	A high caseload for the individual practitioner (> 20).
The care provider takes the initiative on maintaining contacts, and visits patients mainly in their own environment, wherever they are (also when they are hospitalized), the intention being to prevent dropout.	In general, whether contact takes place in the office or at home, involvement ceases (temporarily) after admission has taken place, or if the patient refuses to maintain (long-term) contact. (Normally, there is no contact when the patient is hospitalized.). If patient refuses contact or fails to show up, discharge usually follows.	In general, whether contact takes place in the office or at home, involvement ceases (temporarily) after admission has taken place, or if the patient refuses to maintain (long-term) contact. (Normally, there is no contact when the patient is hospitalized.). If patient refuses contact or fails to show up, discharge usually follows.
Unlimited investment in terms of time (high contact frequency).	Limited contacts, frequency as low as possible.	Limited contacts, frequency as low as possible.
All aid is offered though the ACT team (psychiatric treatment, rehabilitation, assistance with addiction, financial problems, and somatic care).	Only psychiatric care is provided. Addiction, financial problems and other problems are treated by other services.	Only psycho geriatric care is provided. Addiction, financial problems and other problems are treated by other services.
**Disciplines:** Doctor of Medicine or nursing-home doctor (especially for somatic problems) or visiting geriatrist Social worker Psychiatrist Psychologist Community Mental Health Nurse Rehabilitation worker Somatic nurse, Mental Health nurse Homecare worker One of above discipline is specialized in addiction (or double diagnosis)	**Disciplines:** Doctor of Medicine or nursing home doctor Psychiatrist Psychologist, Community Mental Health Nurse	**Disciplines:** Doctor of Medicine or nursing home doctor or visiting geriatrist Psychologist, Community Mental Health Nurse
Each morning there will be a team meeting on all patients in which any necessary appointments are made	Patients are discussed in patient meetings once every six months. Difficult cases are discussed during weekly team meetings.	Patients are discussed in patient meetings once every six months. Difficult cases are discussed during weekly team meetings.
Staff will receive training in ACT methodology	No specific staff training.	No specific staff training.

Table 1 contrasts ACTE working methods with those of CAU [25,26] and [27]), the latter consisting of three teams: a psycho-geriatric team for elderly patients with cognitive problems and two gerontology psychiatric team for elderly patients with psychiatric problems.

Table 1 shows that the main differences between ACTE and CAU will concern team approach including a shared caseload, contact frequency, and the location of care provision. Because care under ACTE will be provided in the patient's living environment, there will often be intensive collaboration with a number of organizations (such as the police in cases of nuisance or homelessness, or with psychiatric hospitals upon admission). Because this group of elderly psychiatric patients is difficult to engage in treatment and may have bad experiences with the care-provision circuit, it is very important than time and energy are devoted to establishing contact with them.

### Outcomes and measurement instruments

Our primary outcome measures will be the number of dropouts (drop-out being defined as no registered contact with the services over a period of 3 months and/or the number of patients discharged out of care). The number of patients who are engaged in care (patients who receive care within 3 months after admission) and patient's psychiatric symptoms, somatic symptoms, and social functioning.

#### Our secondary outcomes measures will be

1. The number of unmet needs,

2. Subjective quality of life,

3. Patients' satisfaction with mental-health care,

4. The number of crisis contacts and (in)voluntary admissions, and the number of admission days. The admission days and crisis contacts were calculated during two periods of observation. The first period was the year before inclusion in the study. The second was the variable observation period ranging till 2 years after inclusion. In both periods, the admission data were standardized as mean number of days per month and crisis contacts as mean number.

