### Hypotheses

Our first hypothesis is that ACTE will decrease the number of patients who drop out of care (number of patients who have no registered contact with the services over a period of 3 months and/or the number of patients discharged out of care). The other primary hypotheses include that ACTE will increase the number of patients engaged in care (patients who receive care within 3 months after admission to the team) and will improve patients' psychiatric, somatic and social symptoms. Secondary hypotheses include that ACTE reduce the number of unmet needs more than CAU does. We also expect an increase in patients' subjective quality of life and in patients' satisfaction with mental-health care. Finally we hypothesize that to a greater extent than CAU, ACTE will reduce the number of crisis contacts, reduce voluntary and involuntary admission rates and reduce length of stay in a psychiatric hospital.

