### Procedure

BavoEuropoort has one ACT team for elderly people (intervention condition). In the control condition (CAU), participants were identified by three general community mental health teams working for elderly people living in the community. Two of these teams focused on patients with psychiatric disorders; the other focused mainly on patients with cognitive impairments. Community mental healthcare professionals from these teams will use a checklist to determine whether all new elderly service-users meet the inclusion criteria. The inclusion of patients started July 2008 and was closed on 1 August 2010.

Figure 1 shows the inclusion flowchart; inclusion criteria are:

1. age 65 year or older;

2. having a severe mental illness (patients with a severe psychiatric disorder, usually psychotic or bipolar disorder or severe depression, leading to a complex combination of psychiatric and social needs).

3. no motivation for treatment (actively or passively resisting treatment; the patient is very difficult to involve in any form of treatment, including treatment by the general practitioner).

4. and 4 problems of the following domains:

- addiction: taking alcohol and drugs taking not in a social context, occasional minimal loss of control of drinking or drugs use or adverse consequences or incapacitated due to alcohol or drug problems.

- somatic problems: all kind of somatic problems, including illness or disability from any cause that limits mobility, impairs sight or hearing, or otherwise interferes with personal functioning.

- daily living activities: the overall level of functioning in activities of daily living: e.g., problems with basic activities of self-care such as eating, washing, dressing, toilet; also complex skills such as budgeting, recreation and use of transport, etc.

- housing: the overall severity of problems regarding the quality of living conditions, accommodation and daily domestic routine, taking into account of the patient's preferences and degree of satisfaction with such circumstances. Are the basic necessities met?

- daytime activities: the overall level of problems regarding the quality of the daytime environment. Limited or no daytime activities. The patients problems are made worse by a lack of daytime activities.

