### Randomization

The patients were referred to BavoEuropoort by general practitioners or other institutions (such as the police or municipal health service), who filled out a form describing the patient's characteristics and current problems. To determine whether the patients fulfilled the inclusion criteria, this form was reviewed using a checklist by the researcher (JS) and clinicians. If the patient did meet the criteria, he or she was allocated a number chronologically by the service administrator. Each number was given to the researcher, who then decided on the condition (intervention or care as usual). This was done on the basis of a previously arranged list of numbers randomized to each of the two conditions (with help from http://www.randomizer.org). To ensure similar numbers in both conditions the pre-arranged list of numbers are based on a block design (block size of four). Inclusion and randomization of patients was done before informed consent was obtained for participation in an interview with the interviewer.

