### Statistical analysis

Analyses will be performed according to the *intention to treat *principle, which means that everyone who is randomized stays in the group in which they were randomized. Statistical package for the social sciences, version 15.0 will be used to analyze the data. The primary outcome measure is the differences between ACTE and CAU regarding the number of patients who were out-of-contact with mental health services. Secondary outcome measures are improvement of psychosocial functioning (total HoNOS 65+ score, total score from baseline to the final interview after 18 months), need-for-care over time (primary outcome measures), the number of crisis contacts and (in)voluntary admissions, and the number of admission days (these last 3 measures will be retrieved from administration files) The interviewer collects the other secondary outcome measures (subjective quality of life and client satisfaction.) Categorical variables shall be analyzed using chi-square tests. Mixed models with repeated measurement were applied for the continuous outcomes. This model will be used because of the ability to include participants with missing data. Missing data at the second and third interview will be imputed with the last carried out interview.

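### For patients new to the service the pre-inclusion year is probably under-recorded, so admission days and crisis contacts should be compared between arms after inclusion, with no before-after claim

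*Protocol article*

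**What the plan says.** All references are to the protocol article.

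- **Who is screened (Procedure).** Professionals in the community teams "use a checklist to determine whether all new elderly service-users meet the inclusion criteria". Eligible patients resist treatment, including from the general practitioner. Under Randomization, "The patients were referred to BavoEuropoort by general practitioners or other institutions".
- **What is counted (secondary outcome measures, item 4).** "The admission days and crisis contacts were calculated during two periods of observation". "The first period was the year before inclusion in the study". For the other, "The second was the variable observation period ranging till 2 years after inclusion". Admission data are put on a days-per-month scale; crisis contacts are given as a mean number.
- **Where the data come from.** Assessment instruments names the electronic patient records. Table 2 names a registration system for crisis contacts and admission days. Statistical analysis says of crisis contacts, admissions and admission days that "these last 3 measures will be retrieved from administration files". No section says whether these files cover care given elsewhere or before the current referral.
- **What is to be shown (Hypotheses).** The expectation is that "to a greater extent than CAU, ACTE will reduce the number of crisis contacts", and likewise admission rates and length of stay. The Discussion repeats the idea of reduction without naming a comparator in that sentence.

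**The concern.** The entry rule selects people who are new to the service, while the first observation period relies on service records from before they were new. A zero in that year may mean that the patient was not yet known, rather than that nothing happened. After inclusion the patient is known and events are more likely to be on file.

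A hypothesis of greater reduction, together with a matched pair of pre and post periods, reads most naturally as a difference in change from the pre-year. Two things are then at stake. First, a change within one arm mixes treatment effect with better recording, and putting both periods on a monthly scale does not remove this. Second, subtracting a weakly informative pre-year value adds noise. The trial recruited 64 patients, and its own Discussion says that power is a problem.

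**Working it through.** **The plan's own figure.** The article gives no event rate, coverage or sample size for these outcomes. Its one sample size, 50 per condition, concerns remaining in care. It reproduces, taking alpha as two-sided: 2 × (1.960 + 1.036)² / 0.6² = 49.9, so 50. Nothing below depends on it.

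**Inputs from the article.** Pre-period 12 months; post-period variable, up to 24 months; 64 recruited; two arms with blocks of four.

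**Assumed inputs.** The share c of true pre-year events that is on file; full recording after inclusion; the pre-post correlation r; and k = SD(pre) / SD(post).

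**Step 1: change within an arm.** If the true rate is unchanged, the recorded rate appears to rise by a factor 1/c: none at c = 1, 2-fold at c = 0.5, 4-fold at c = 0.25.

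As an illustration, assume a true pre-year rate of 1.0 per month in both arms, falling to 0.8 under CAU and 0.6 under ACTE. Recorded change = post rate − c × 1.0.

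| c | CAU change | ACTE change | ACTE − CAU |
|---|---|---|---|
| 1 | −0.20 | −0.40 | −0.20 |
| 0.75 | +0.05 | −0.15 | −0.20 |
| 0.5 | +0.30 | +0.10 | −0.20 |
| 0.25 | +0.55 | +0.35 | −0.20 |
| 0 | +0.80 | +0.60 | −0.20 |

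At c = 0.5 a true fall in both arms is recorded as a rise in both. The last column does not move.

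**Step 2: bias in the randomised contrast.** The pre-year precedes allocation, so c is the same in both arms in expectation. A simulation without treatment effect confirms this. It used 64 patients, 32 per arm, with patient rates varying around a mean of 3 events a year and 18 months of follow-up (all but the 64 assumed):

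| c | mean difference in change | SD |
|---|---|---|
| 1 | −0.0001 | 0.046 |
| 0.5 | −0.0008 | 0.0495 |
| 0.25 | 0.0008 | 0.057 |
| 0 | −0.0011 | 0.069 |

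There is no bias, but precision falls. That loss is baseline information that was never recorded, so adjustment cannot bring it back.

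**Step 3: change against adjusted comparison.** With the follow-up variance set to 1, the change has variance 1 + k² − 2rk and the baseline-adjusted comparison 1 − r². The ratio is

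(1 + k² − 2rk) / (1 − r²) = 1 + (k − r)² / (1 − r²).

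It cannot fall below 1, apart from the small cost of estimating the slope.

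| k | r = 0.1 | r = 0.3 |
|---|---|---|
| 1 | 1 + 0.81/0.99 = 1.82 | 1 + 0.49/0.91 = 1.54 |
| 0.5 | 1 + 0.16/0.99 = 1.16 | 1 + 0.04/0.91 = 1.04 |
| 0.25 | 1 + 0.0225/0.99 = 1.02 | 1 + 0.0025/0.91 = 1.00 |

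If the pre-year is almost empty, change is practically the post rate and the ratio tends to 1. Under-recording is likely to make k small, so the lower rows fit the concern better than the first.

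**The case against.** The strongest reply is that no before-after effect is planned. The hypothesis is relative to CAU, Statistical analysis names no pre-post test, and the secondary outcomes section only says that two periods were calculated. The pre-year might serve as description or as a covariate, and how it enters a model is commonly left to an analysis plan. This stands in part: the article does not state a within-arm test. But reduction to a greater extent, set beside paired pre and post periods, invites a difference in change, and the Discussion's wording leaves room for a before-after reading.

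A reader might go further and infer any of the following, which the article does not support:

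- **That the question about reduction has a false baseline and cannot be answered.** The question is posed against CAU, and steps 1 and 2 show that contrast intact.
- **That the centre's own files hold little on these patients.** The files are not described as centre-only. New may mean new to the team. The centre runs clinical settings for voluntary and involuntary admission in its catchment area, and the intervention section says that patients may have had bad experiences of care. Resisting treatment does not imply an empty crisis or involuntary-admission record. Under-recording is probable, not established.
- **That the problem extends to the number of admissions.** The two periods are stated for admission days and crisis contacts only.
- **That the variance penalty is 1.82.** That requires equal SDs, which sits badly with a truncated pre-year.

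**Conclusion.** The point holds in a limited form. The pre-inclusion year is probably under-recorded for patients new to the service, by an amount the article gives no means of judging. A change from that year within either arm is therefore not interpretable as a treatment effect: an unchanged rate would look 2-fold higher if half the earlier events were on file.

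The ACTE–CAU contrast remains unbiased. For that contrast the choice between change and adjustment affects precision only, with a variance ratio between about 1 and 1.82 at r = 0.1 according to k. The values of c, r and k, and full recording after inclusion, are assumptions. The matter is minor: it concerns secondary outcomes, and the remedy is nearly free.

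**What to change.** 1. In item 4 of the secondary outcome measures and in Statistical analysis, define the effect on admission days and on crisis contacts as the between-arm comparison of post-inclusion rates per month of observation.
2. Use the pre-year rate only as a covariate, together with an indicator of registration before inclusion if the files provide one.
3. State what the registration and administration files cover for the year before inclusion.
4. Word the hypothesis as fewer crisis contacts and admission days than under CAU, and make no claim of reduction from the year before.

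The cost is wording in three sections and at most one extra variable from existing records. What is given up is a within-patient before-after statement, which these data cannot safely carry while file coverage is unknown.

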#### Assessment instruments

Measurements will be made at three points of the study: at baseline, and after 9 and 18 months. In the meantime, the patients will be treated according to the ACT model or CAU. The same instruments will be used for all three measurements.

The following data will be obtained from the patient's electronic records:

- Demographic and socio-economic characteristics (including gender, age, ethnicity),

- Data concerning living situation, homelessness, employment, and education,

- The psychiatric diagnosis,

- Use of medication,

- Deaths (included suicide) and

- Data on the number of patients who are engaged in care, the number of dropouts and the time between the start of the treatment and dropout. Also the number of crisis contacts and voluntary and involuntary admissions, and the length of stay of admission will be collected.

Using assessment instruments, the following data will be collected:

- Psychosocial functioning (psychiatric, somatic and social symptoms/functioning) by means of the health of nations outcome scale for the elderly (HoNOS 65+, Dutch version) [29,30]

- Care needs by means of the abridged Camberwell assessment of needs elderly (CANE, short version, Dutch version [31,32].

- Quality of life by means of the quality of life (QoL, abridged version of the Manchester short assessment of quality of life; [33,34].

#### HoNOS 65+

The purpose of the HoNOS 65+ [29,30] is to describe the psychological and social functioning of elderly psychiatric patients, and to provide insight into the severity of various psychosocial problems by identifying changes in relevant areas of life.

The HoNOS 65+ can be used to measure the effect of treatment. It consists of 12 items in four sub-scales: behavior disturbance (items 1-3), impairment (items 4-5), symptoms (items 6-8), and social problems (items 9-12). A Dutch addendum to the HoNOS 65+ contains three questions on problems resulting from manic-depressive disorder, motivation for treatment, and medication compliance. These items have not been validated [35]. All items will be completed on a 5-point Likert scale from 0 (no problem), 1 (minor problem), 2 (mild problem), 3 (moderate problem), to 4 (severe problem). The Dutch version of the HoNOS 65+ has been shown to be properly valid [36].

#### Cane

The CANE [31,32] establishes whether an elderly person has problems and/or care needs in various areas of life, and, if necessary, whether adequate effective care is being given. It consists of 26 questions on items such as needing a diet, daily activities, and psychotic symptoms. Care needs are scored in the following manner: 0 (no need), 1 (met need), and 2 (unmet need).

#### QoL

Quality of life will be measured using the QoL scale, which has shown itself to be well suited to measuring satisfaction in the chronic psychiatric target group [33,34]. Dealing with patients' subjective perceptions with respect to quality of life, the scale consists of six elements covering patients' satisfaction with their 1.) life as a whole, 2.) living situation, 3.) personal relationships 4.) physical health, 5.) mental health and 6.) financial situation. Per item, the researcher will ask the patient to award a score on a 7-point Likert scale ranging from 1 (bad or not at all satisfied) to 7 (good and very satisfied).

#### Satisfaction with the care-provider

The QoL scale will be extended with one question on patients' satisfaction with their treatment. This will be taken from the satisfaction questionnaire [34], and, like all answers in the QoL, be rated as a single question on a 7-point Likert scale.

